#### Experimental groups

2.2.2

Patients will be divided into 2 groups (29 per group).

Group 1: will use a regimen with *Colgate Total 12* toothpastes + *Plax* mouthwashes + *Colgate Ultrasoft* toothbrushes (commercially available regimen);Group 2: will use *Colgate Cavity Protection* Toothpastes + *Colgate Ultrasoft* toothbrushes.

Volunteers will be instructed to use only their assigned products during the study period. These will be re-supplied at regular intervals. Volunteers will return with their assigned products to the study site before receiving new products.

#### Sample calculation

2.2.3

The sample size was calculated to assure a test power greater than 95% and a significant level of α = 0.05. By using the data from Parizi et al,^[20]^ we estimated an effect size of 1.10. Figure 2 shows the plot of the test power as a function of the total sample size assuming normal data distribution, 2 tails and 2 independent groups.

**Figure 2 F2:**
[figure not shown]
Shows that 23 subjects per group is sufficient to detect significant differences with a test power of 95%. Assuming a lost to follow up of 20%, 29 subjects are required in each group.

#### Randomization

2.2.4

To randomly distribute the volunteers in the 2 groups, a random sequence generator program (https://www.randomiz er.org/tutorial/) will be used and the 6-member randomization option will be selected. Opaque envelopes will be identified with each number and inside it a sheet containing the information of the corresponding experimental group will be inserted according to the generated order. The envelopes will be sealed and will remain sealed in numerical order in a safe place until the time of the surgeries. The generation of the sequence and the preparation of the envelopes will be performed by a person who is not involved in the study.

### Clinical evaluations

2.3

#### Calibration of examiners

2.3.1

For the training and calibration process of the examiners, each will classify the visible plaque index, simplified oral hygiene index and gingival bleeding index using photographs and a sample of ten volunteers, who will not be involved in the main study. Intra-examiner reproducibility will be determined by repeating the examination of these volunteers after a 1-week interval until reaching a nearly perfect Kappa agreement coefficient. In cases of nonagreement between the examiners regarding the results, a discussion will be held to reach a consensus and this new evaluation will be considered definitive.

#### Halitosis evaluation

2.3.2

An experiment examiner will perform training exercises to maximize the reproducibility of measurements. Then, 10 volunteers with positive halitosis will be evaluated using the Breath Alert device. These individuals will be excluded of the study. The intraclass correlation coefficient will be calculated, and the intra-examiner agreement with regard to the halitosis must be ≥0.90.

### Interventions

2.4

#### Initial Instructions

2.4.1

The volunteers and their caregivers will be invited to a lecture with the aim of clarifying the importance of oral hygiene and motivating tooth brushing. Written clarifications will also be given in the form of an illustrative pamphlet. The volunteers will be trained in the technique through supervised brushing in front of a mirror. There will be no restrictions regarding diet habits during the course of the study. Upon completion of the study, subjects will be instructed to return all used products.

In return appointments, the volunteers will receive oral hygiene motivation, which will involve a verbal clarification of the importance of oral hygiene, written instructions in the form of an illustrative pamphlet and further training on the brushing technique.

#### Evaluation of biofilm index

2.4.2

After the hygiene instructions, the volunteers will be submitted to examinations by 2 blind examiners. Gingival status will be evaluated through a visual examination with the aid of a millimeter probe (height and width). A World Health Organization (WHO) probe will be used for the determination of the visible plaque index, gingival bleeding index and simplified oral health index at baseline, as well as after the use of the brush.

Visible plaque index – Silness and Loe – 0: Absence of visible biofilm; 1: Non visible biofilm that can be removed with the probe; 2: Biofilme that is visible after drying; 3: Abundant biofilm, even without drying.Gingival bleeding index – 0: Sound; 1: Red gingival margin, without bleeding on probing; 2: Red gingival margin, with bleeding on probing; 3: Bleeding after jet of compressed air.Simplified oral hygiene index – Greene and Vermillion, 1964: After revealing the plaque with the use of a stain, the index surfaces will be scored as follows: 0: nonstained surface; 1: only the region that is close to the gingival margin is stained; 2: half the surface is stained; 3: the entire surface is stained. The sum of the surface scores will be calculated and divided by the number of evaluated surfaces to obtain the simplified oral hygiene index.

After these evaluations, the volunteer will be submitted to prophylaxis with a rubber cup, Robinson brush, prophylactic paste, and dental floss. The procedures will be administered according to the study protocols.

#### Halitosis index

2.4.3

##### Coated tongue index

2.4.3.1

The tongue surface will be divided into nine parts and each part will be received a score: 0—absence of tongue coating; 1—presence of tongue coating, but visible papillae; 2—thick tongue coating, with nonvisible papillae. The total will be determined by summing the scores for each one of the 9 parts of the tongue, then dividing by 18 and multiplying by 100 to obtain the final index (0%–100%).^[21]^

##### Salivary flow analysis

2.4.3.2

The volunteer will be instructed to sit in a chair during 5 minutes, in silence, with eyes open. A piece of sterile, disposable, hyperboloid, silicone rubber (Saúde Bucal) will be used to stimulate chewing for 5 min and the saliva will be deposited in a millimeter recipient at 30 seconds intervals for 5 min. The volume of produced saliva will be measured and flow velocity will be calculated as millimeters per minute. The reference values for normal salivary flow will be: 1 to 2 ml min^−1^; diminished: 0.7–0.9 ml min^−1^; hyposalivation: <0.7 ml min^−1^ and severe hyposalivation: ≤0.3 ml min^−1^.

##### Salivary pH

2.4.3.3

The device for carrying out this assessment will be a portable digital pH meter (DIGIMED DU-02). The pH meter will be calibrated with each new Reading, using standard solutions with pH 6.86 and 4.00. Stimulated saliva will be collected in disposable plastic cups. The measurement of salivary pH will be determined immediately after the collection of the saliva. The pH meter will be cleaned with distilled water before and after each reading. The following reference values will be used: ≥5 = normal; 3.99 to 4.99 = borderline; and ≤4 = low.

#### Toothbrush instructions

2.4.4

Two undergraduate dentistry students will perform hygiene instructions. Volunteers will be told to moisten the brush with cold, running water and place a fixed quantity of toothpaste (0.5 cm) on the bristles. In Group 1, the subjects will be instructed to rinse with *Colgate Plax* (mouthwash) after brushing. Brushing will be performed and taught, using the modified Bass technique, starting on the right side of the maxillary arch. Using a chronometer, brushing will be performed for 30 seconds in each quadrant (15 seconds on the buccal side and 15 seconds on the lingual side), totaling 2 minutes for the entire mouth. The alarm on the chronometer will go off every 15 seconds. If the volunteer has already finished brushing in the respective quadrant, he/she can initiate brushing in the next quadrant. To maintain the blinding of the evaluations, the brushing and evaluations will be performed in different locations. After completing the brushing procedure, the volunteer will completely rinse his/her mouth to ensure the removal of all residual toothpaste.

### Discomfort and satisfaction reports by adolescents regarding the regimens (secondary outcome)

2.5

Discomfort will be evaluated immediately after the use of each brush. For such, the Wong-Baker facial scale will be used, which is composed of 6 figures. The first is a smiling face, followed by increasing degrees of discomfort through to the last face, which is sad. The volunteer will be instructed to indicate the face that most closely corresponds to the experience of using the brush.

During follow-ups, the volunteer will be asked to state his/her degree of satisfaction with the use of the brush during the period. Satisfaction will be classified as follows: 0- excellent; 1- good; 2- acceptable; 3- poor. The volunteer will also be asked about possible side effects and complaints related to the use of the brush. This evaluation will be performed without the presence of the examiners to enable the participant to give his/her honest opinion.

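### The discomfort, satisfaction and side-effect items ask about the brush, which is the same in both arms, and do not name the mouthwash, so they are poorly aimed at the regimen comparison

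*Protocol article*

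**What the plan says.** Section 2.2.2 (Experimental groups) sets the contrast. Group 1 uses Total 12 toothpaste with "Plax* mouthwashes + *Colgate Ultrasoft* toothbrushes (commercially available regimen"). Group 2 uses "Colgate Cavity Protection* Toothpastes + *Colgate Ultrasoft* toothbrushes". The brush is common to both; the toothpaste differs, and only Group 1 has a mouthwash.

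Section 2.5 is headed "Discomfort and satisfaction reports by adolescents regarding the regimens (secondary outcome"). Under that heading:

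- Timing of discomfort: "Discomfort will be evaluated immediately after the use of each brush".
- Content of discomfort: the volunteer is to "indicate the face that most closely corresponds to the experience of using the brush".
- Satisfaction, at follow-ups: the volunteer is to "state his/her degree of satisfaction with the use of the brush during the period".
- Side effects, at follow-ups: the question covers "possible side effects and complaints related to the use of the brush".

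On the order of use in Group 1, section 2.4.4 (Toothbrush instructions) states that "the subjects will be instructed to rinse with *Colgate Plax* (mouthwash) after brushing".

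Section 2.7 lists discomfort and satisfaction as secondary outcomes. Section 2.8 dichotomizes discomfort, enters treatment as an independent variable, and describes the satisfaction item as being about the treatment, to be reported descriptively.

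**The concern.** The heading and the analysis promise a comparison of regimens, but the items are about the component that the regimens share. The phrase about each brush also suggests a comparison of brushes, which this trial does not make. The Discussion (section 3) does the same when it motivates these outcomes by a lack of studies comparing toothbrushes.

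What is at stake is the patient-centred part of the trial. The abstract says that participants' acceptability will help to confirm the effectiveness of the protocols. If the two arms give similar answers, a reader is likely to conclude that the fuller regimen is as acceptable and as well tolerated as brushing alone. Answers about the brush would not support that conclusion. The side-effect question is the only one the article describes, and section 4.3 anticipates no adverse effects, so a complaint about the mouthwash may have no prompted route into the data.

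**Working it through.** The plan gives no figure that bears on this point, so the check sets the sections side by side.

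**Step 1. What differs between the arms (section 2.2.2)**

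| Component | Group 1 | Group 2 | Differs? |
|---|---|---|---|
| Toothbrush | Ultrasoft | Ultrasoft | No |
| Toothpaste | Total 12 | Cavity Protection | Yes |
| Mouthwash | Plax | none | Yes |

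**Step 2. What each item names (section 2.5)**

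| Item | Brush | Toothpaste | Mouthwash |
|---|---|---|---|
| Discomfort (timing and content) | named | not named | not named |
| Satisfaction | named | not named | not named |
| Side effects and complaints | named | not named | not named |

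All three items name the one component that does not differ. None names either of the two that do. No other section of the article redirects the items to the whole regimen.

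**Step 3. By what route each real difference could still reach the answers**

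- *Toothpaste.* Section 2.4.4 has 0.5 cm of toothpaste placed on the bristles and two minutes of brushing. Taste, foam or irritation can therefore colour the experience of using the brush. This route is open but indirect.
- *Mouthwash, by wording.* No item refers to it. It is recorded only if a participant goes beyond the question.
- *Mouthwash, by timing.* Section 2.4.4 places the rinse after brushing, and section 2.5 scores discomfort straight after brush use. Read literally, the score can come before the rinse. The 29 participants in Group 1 are the ones affected.

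**Step 4. How the answers are used (section 2.8)**

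- Discomfort is modelled with treatment as an independent variable, so a regimen effect is intended.
- Satisfaction is called satisfaction with treatment, which does not match the object given in section 2.5, and is only described.
- No analysis is named for side effects.

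The analysis therefore treats as regimen outcomes what the items collect as brush outcomes. A statistical analysis plan could not repair this, because it cannot recover answers to questions that were not asked.

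**The case against.** The strongest reply is that the wording is loose and the design is sound. The article uses brushing as shorthand for the whole regimen: the abstract and Introduction call the two product sets brushing regimens, and the mouthwash instruction itself sits under a heading about the toothbrush. The article also condenses a fuller protocol and paraphrases the questions, so the prompts actually put to adolescents may be broader. This stands in part. It is a reason to call for reconciliation, and it limits how firmly one can say what participants will be asked. It does not remove the point, because section 2.5 states the object of every item, each time as the brush, and a reader following the published text would ask about the brush.

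A second reply is that the items are not blind to the regimen, because the assigned toothpaste is on the bristles. This stands fully. A reader might infer that the expected difference between arms is zero by construction, that the items cannot compare the regimens at all, or that a test would have power no better than its 5% error rate. The documents do not support any of these. Each assumes that participants answer about the brush with no influence from the toothpaste. The power statement also has no calculation behind it, and it could not apply to satisfaction, which is only described, or to side effects, for which no test is named.

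A third reply is that the stakes are modest. This also stands: discomfort and satisfaction are secondary, and section 2.7 does not list side effects among the outcomes.

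**Conclusion.** The point holds as a mis-targeted measurement in secondary outcomes. The discomfort, satisfaction and side-effect items are worded around a brush that both arms share. They can reflect the toothpaste only through the brushing experience. They omit the mouthwash, and discomfort may be scored before it is used. A null result would say little about the acceptability or tolerability of the Group 1 regimen.

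Its size is three patient-reported items across all 58 participants, with the mouthwash gap confined to the 29 in Group 1. The primary outcomes are untouched. The loss of sensitivity cannot be quantified, because the documents give no expected discomfort rates and no basis for judging how far toothpaste or mouthwash effects would spill over into answers about the brush.

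The conclusion assumes that the items are asked substantially as section 2.5 describes them. If the actual questionnaire already refers to the whole regimen, what remains is an inconsistency to correct in the text.

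**What to change.** 1. Word all three items for the participant's assigned products: toothpaste, toothbrush and, if given, mouthwash.
2. Ask about discomfort once all assigned products have been used, which in Group 1 means after the rinse.
3. In section 2.5, replace the reference to each brush with the assigned regimen.
4. Reconcile sections 2.5 and 2.8 so that the outcome collected is the outcome analysed, and align the toothbrush wording in the Discussion.

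Recording side effects separately by component would help interpretation but is optional.

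Before the first participant, the cost is rewording a short questionnaire, plus any report to the ethics committee that section 4.1 requires. No extra visits or staff are needed. Once answers have been collected, they cannot be corrected. In that case the report should describe these outcomes as reports on brush use and draw no conclusion about the acceptability of the mouthwash.

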### Questionnaire of socioeconomic and individual characteristics

2.6

The volunteers and their caregivers will answer a questionnaire addressing personal data, general health and oral health. The socioeconomic and individual characteristics of the volunteers, such as the use of fluoride toothpaste, the use of dental floss, frequency of visits to the dentist, hygiene regimen performed by the volunteer, frequency, and content of the diet will be questioned. Evaluation of caries experience using the Decayed, Missing due to caries, and Filled Permanent Teeth (DMFT) index and evaluation of the presence of active carious lesions on smooth surfaces;

### Outcomes measures

2.7

All variables will be evaluated by the same 2 examiners, at the baseline, 1, 3, and 6 months. The primary outcomes of the study are: efficacy of a commercially available regimen vs brushing alone on established frequency of biofilm index and gingival bleeding. The secondary outcomes of the study are: halitosis, discomfort and satisfaction, socioeconomic characteristics. Information on gender (male/female), race, age (in years), general and oral health educational background (from illiterate to full graduate) will also be collected.

### Statistical analysis

2.8

Data will be submitted to descriptive statistical analysis to demonstrate the distributions frequency of biofilm index and gingival bleeding (mean and standard deviation) and qualitative (frequencies and percentages). For the analysis of the data on discomfort, the outcome will be dichotomized as 0 (no discomfort) or 1 (discomfort). Treatment will be used as an independent variable, along with other variables that could influence the outcome, such as sex, age, previous visits to the dentist and caries experience. The responses with regard to satisfaction with the treatment will be evaluated descriptively.

Then, the appropriate statistical tests will be applied for each specific analysis. In all tests, the significance level of 5% probability or the corresponding *P*-value will be adopted. All analyses will be performed using the statistical software SAS for Windows, version 9.1.

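### Two primary outcomes, with no primary index, visit or success rule and 5% for every test, leave the primary error rate above 5% if any significant result counts

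*Protocol article*

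**What the plan says.** - **Primary outcomes (section 2.7, Outcomes measures).** The primary aim is efficacy of the regimen against "brushing alone on established frequency of biofilm index and gingival bleeding". All variables are evaluated at baseline and at 1, 3 and 6 months, and no visit is singled out.
- **Indices (section 2.4.2, Evaluation of biofilm index).** A probe is used for "determination of the visible plaque index, gingival bleeding index and simplified oral health index at baseline" and again after brush use. Two of these three indices, visible plaque and simplified oral hygiene, score biofilm. Only the simplified oral hygiene index comes with a rule that turns surface scores into one value per participant.
- **Error rule (section 2.8, Statistical analysis).** "In all tests, the significance level of 5% probability" is adopted. The section lists no individual tests for the primary outcomes; it refers only to appropriate tests for each analysis.
- **Sample size (section 2.2.3, Sample calculation, and the Figure 2 caption).** "The sample size was calculated to assure a test power greater than 95" per cent, at alpha 0.05. The inputs are "we estimated an effect size of 1.10" and "assuming normal data distribution, 2 tails and 2 independent groups". The caption adds that "23 subjects per group is sufficient to detect significant differences with a test power of 95" per cent, and then: "Assuming a lost to follow up of 20%, 29 subjects are required in each group". The outcome, index and visit behind the effect size are not named.

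**The concern.** The term biofilm index does not identify one variable, and the primary outcomes have three post-baseline visits with no order among them. Nothing in the text says whether efficacy needs one significant result, both outcomes, or a particular visit. With 5% applied to every test, a favourable result on either biofilm index or on bleeding, at any visit, could be reported as the primary finding, and the choice could be made after the data are seen.

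Two things are at stake, and they belong to different success rules. If any one success is enough, the false-positive rate for the primary claim exceeds 5%. If both outcomes must succeed, that rate is controlled, but the chance of success is lower than the single-comparison power for which the trial was sized.

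**Working it through.** **Inputs.** From section 2.2.3 and the Figure 2 caption: d = 1.10, two-sided alpha 0.05, two independent groups, 23 evaluable per group, 20% loss, 29 enrolled per group. From sections 2.7 and 2.4.2: two primary outcomes, three indices, three post-baseline visits. From section 2.8: 5% in every test. The documents give no correlation between indices or visits, so a range is assumed.

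**1. The plan's own figure.** Two-sample t-test, noncentrality d × √(n/2) = 1.10 × √(23/2) = 3.73, 44 degrees of freedom:
- n = 23 per group: power 95.4%; n = 22: 94.6%. So 23 is the smallest size that reaches 95%.
- 23 / (1 − 0.20) = 28.75, rounded up to 29.

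The sample size reproduces. It covers one two-group comparison at 5%.

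**2. How many primary tests?** The protocol does not say. Four readings fit sections 2.4.2 and 2.7:
- 2 tests: one per outcome (for example one repeated-measures comparison each, or one visit).
- 3 tests: one per index.
- 6 tests: 2 outcomes × 3 visits.
- 9 tests: 3 indices × 3 visits.

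**3. Chance of at least one false positive if any significant result counts.** For independent tests it is 1 − 0.95^k. For correlated tests, standard normal statistics were simulated. The correlation r applies between outcomes or indices and also between visits; for a pair that differs in both, the two values are multiplied.

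| Tests (k) | Independent | r = 0.5 | r = 0.8 |
|---|---|---|---|
| 2 | 1 − 0.95² = 9.8% | 9.1% | 7.8% |
| 3 | 1 − 0.95³ = 14.3% | 12.5% | 9.8% |
| 6 | 1 − 0.95⁶ = 26.5% | 22.0% | 14.9% |
| 9 | 1 − 0.95⁹ = 37.0% | 29.4% | 18.4% |

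At r = 0.9 the last two rows are still about 12% and 14%.

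**4. Joint power if both primary outcomes must be significant at one visit.** The assumptions are 23 per group and d = 1.10 for both outcomes.
- Independent: 0.954 × 0.954 = 91.1%.
- r = 0.5 to 0.8: about 93% to 94% by normal approximation. Simulated t-tests give slightly less, 92% to 93%.

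Alpha is not inflated under this rule, but joint power is below 95%.

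**5. Power if alpha were split instead.** Bonferroni for two tests uses 0.05/2 = 0.025 each. With d = 1.10, power per test is 91.6% at 23 per group, and 96.8% if all 29 per group are evaluable.

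**The case against.** The strongest reply is that section 2.8 lists no tests, and that model choice and multiplicity handling are often left to an analysis plan, which is not shown here. One repeated-measures comparison per outcome would leave two or three tests, and the inflation would then be modest. Repeated scores in the same mouths are also correlated, so the independence figures are upper bounds.

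Much of this stands. A reader might infer that the trial will run 6 or 9 primary tests; the documents do not say so, and those counts are readings, not facts. But the protocol is not silent on alpha. It fixes 5% for every test next to two primary outcomes, so a later adjustment would depart from its own sentence. Even with two tests the rate is about 8% to 10%.

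A reader might also infer that the 95% power holds for one test only. That is not supported: every unadjusted 5% test has 95.4% power at 23 per group if d = 1.10 applies to it. Power falls only if alpha is split or both outcomes must succeed, and the split costs little if few participants are lost. Nor does the protocol claim a 5% overall error rate, so it does not contradict itself there.

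**Conclusion.** The point holds in limited form. The sample size arithmetic is correct. The defect is that two primary outcomes stand without a primary index, visit or success rule, under a flat 5% rule.

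If any success counts, the primary error rate is above 5% on every reading of the text: from about 8% (two tests, correlation 0.8) to 37% (nine independent tests). The lower part of that range applies if visits are not tested separately. If both outcomes must succeed at one visit, the problem is not alpha but a joint power of about 91% to 94%. The two harms are alternatives and do not add up.

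These sizes rest on an inferred number of tests, assumed correlations and, for power, d = 1.10 applying to each outcome. A reader might infer that any index and visit chosen as primary would keep 95.4% power. The documents do not support that, because they tie d = 1.10 to no index or visit.

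**What to change.** Before any data are seen, amend the protocol, the analysis plan if there is one, and the registry entry as follows:

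1. Name one biofilm index at one visit as the primary endpoint. The simplified oral hygiene index at 6 months is a reasonable example, since it alone has a stated participant-level score. The sponsor may prefer another; what matters is that one is named.
2. Test gingival bleeding at the same visit second, at 5%, only if the first test is significant. This fixed sequence keeps the error rate across the two tests at 5% without splitting alpha.
3. Label the other biofilm index and the remaining visits secondary.
4. State which outcome, index and visit d = 1.10 belongs to, and say that the 95% power applies to the first test only if that effect size holds for it.

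Two co-primary outcomes or an alpha split would also repair the plan, with the power consequences shown above. The recommended change is wording only and adds no participants to the 58. Its downside is that fewer comparisons can be called confirmatory, and bleeding cannot be claimed if the biofilm test fails.
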